### 3.5 Dose selection

The classical texts did not use the metric system; doses were described using traditional units such as *ratti* and *karsha*. According to *Bhāvaprakāśa Nighan.t.u*, the dose of *Brahmi* Choorna ranges from 4 to 8 *ratti*, where 1 *ratti* is approximately 125 mg, corresponding to 500–1,000 mg (35). The *Sharangadhara Sam.hita* mentions a general dose of 1 *Karsha* (≈12 g) (36). For modern clinical application and standardization, the Ayurvedic Pharmacopoeia of India (API) recommends 1–3 g of *Brahmi* Choorna. (37) Considering the intervention duration of 2 months in this study, a lower-end dose of 500 mg per day was selected to ensure safety while remaining within the classical and standardized dose range. This dose aligns with both traditional guidance and contemporary clinical practice, ensuring participant safety without compromising potential efficacy.

### 3.6 Choice of comparator

Cognitive Behavioral Therapy (CBT) has been chosen as the comparator treatment due to its well-documented efficacy in alleviating symptoms of PMS. However, there is evidence that symptom recurrence can occur after discontinuation of CBT. To enhance the durability and breadth of therapeutic effects, this study introduces *Brahmi* as an adjunct therapy. Brahmi’s known cognitive, neurochemical, and gut-regulating effects may provide complementary benefits when used alongside CBT.

In this trial, the intervention group will receive CBT along with a 500 mg *Brahmi* tablet, while the comparator group will receive CBT with a placebo tablet identical in appearance. This design will help to understand the combined effect of CBT and *Brahmi* in enhancing symptom control and functional outcomes.

### 3.7 Intervention modifications

If participant misses their scheduled morning dose of the *Brahmi* tablet or the placebo tablet, the following protocol will be implemented:

Same-day missed dose: If the participant realizes the missed dose within the same day, they may take the dose in the evening, provided it is at least 6 h after the previous dose.Next-day missed dose: If the missed dose is realized the following day, the participant should skip the missed dose and resume the regular dosing schedule at the next scheduled time.

Regarding missed Cognitive Behavioral Therapy (CBT) sessions, if a participant is unable to attend a scheduled session, the following options are available:

Rescheduling: The session may be rescheduled to the next available day, ensuring that the session occurs within 24 h of the original appointment.Preponing: With prior notice, the session may be conducted earlier than the scheduled time, provided it is within the same week.

These flexible scheduling options aim to accommodate participants’ availability and minimize disruption to their treatment plan.

### 3.8 Protocol adherence criteria

#### 3.8.1 Adherence to *Brahmi* intake

Medication consumption: participants will be considered adherent if they consume at least 80% of the prescribed *Brahmi* tablets during the intervention period.Pill count verification: compliance will be objectively monitored by pill counts conducted at each follow-up visit. Any discrepancy will be documented in the case record form.Missed doses: participants will be instructed to record any missed doses in a provided diary. Repeated non-adherence (e.g.,> 20% missed doses) will be flagged as protocol deviation.Correct usage: intake of the drug must align with provided instructions, i.e., correct dosage schedule and proper storage.

#### 3.8.2 Adherence to CBT participation

Attendance requirement: participants will be considered adherent if they attend at least six sessions (75%–80%) of the scheduled CBT sessions.Session documentation: attendance will be recorded by the therapist/facilitator after each session, and non-attendance will be followed up by reminder calls.Engagement in sessions: active participation (completion of exercises, discussions, and assignments) will also be documented to assess qualitative adherence.Make-up sessions: if participants miss a session, opportunities for catch-up or supplementary guidance will be offered, ensuring minimal loss of therapeutic continuity.

#### 3.8.3 Combined adherence monitoring

Overall protocol adherence will be defined as meeting both the minimum thresholds for *Brahmi* intake (≥ 80%) and CBT session attendance (≥ 75%–80%).Participants failing to meet either criterion will be considered partial adherents, and this will be documented in adherence logs for sensitivity analysis during final data evaluation

### 3.9 Adherence-improving strategies

To ensure compliance with both the medication and CBT interventions, the following strategies will be employed:

#### 3.9.1 Follow-up sessions

Participants will be called for follow-up sessions during both screening and treatment phases, where the importance of adherence to study protocols will be reinforced.

#### 3.9.2 Medication guidelines

Clear instructions will be provided regarding dosage schedule, storage conditions, and the necessity of taking tablets intact.Procedures for managing a missed dose will be explained.Participants will be reminded about the objectives and expected benefits of the intervention.

#### 3.9.3 Pill count monitoring

Pill counts will be conducted and documented at every study visit to objectively assess medication adherence.

#### 3.9.4 CBT session attendance

Attendance at each CBT session will be documented through session logs and trainer records.Missed sessions, along with reasons, will be recorded.Therapists will maintain brief notes on participant engagement to ensure fidelity of the intervention.

#### 3.9.5 Adherence reminders

At each visit, participants will be reminded of the significance of adhering to study requirements for reliable outcomes.

#### 3.9.6 Reporting issues

Participants will be encouraged to immediately contact the study center in case of any difficulties with medication intake or CBT participation, including side effects or scheduling challenges.

### 3.10 Rescue medication

In case of nausea or vomiting, *Dhanwantharam Gulika* (a polyherbal tablet, traditionally indicated for gastrointestinal disturbances) will be administered. For diarrhoeal episodes, either *Mustarishtam* (a fermented herbal preparation with Cyperus rotundus, used for digestive disorders) or *Kutaja Arishtam* (containing Holarrhena antidysenterica, widely used for diarrhoeal disorders) will be provided, depending on the clinical presentation. For pain or abdominal cramps, participants will be managed with *Hinguvachadi* Tablet (a classical Ayurvedic formulation for abdominal cramps); if symptoms remain refractory, they will be referred to a modern medical practitioner and may be permitted Paracetamol (up to 500 mg as required). For insomnia or heightened anxiety, non-pharmacological measures such as breathing exercises will be recommended. All formulations will be procured from a GMP-certified manufacturer with Quality of Analysis report and use of any rescue medication will be documented for each participant and considered during analysis. No hormonal or psychotropic rescue medications will be allowed during the study period.

## 4 Outcome measures

### 4.1 Exploratory primary outcomes

• Changes in PMS symptom severity, as measured by the Daily Record of Severity of Problems (DRSP) across two intervention cycles.

• Changes in quality of life, as assessed by the Quality-of-Life Enjoyment and Satisfaction Questionnaire Short Form (Q-LES-Q SF 12) from baseline to post-intervention.

### 4.2 Exploratory secondary outcomes

• Changes in functional impairment, as measured by the Sheehan Disability Scale (SDS) total and domain-specific scores, reflecting work, social, and family functioning.

#### 4.2.1 Participant timeline

Participants enrolled in the study will undergo a structured series of visits spanning multiple menstrual cycles. During the first visit, personal history, socio-demographic information, and detailed menstrual history will be recorded. Participants will also complete the Patient Health Questionnaire-9 (PHQ-9) to assess depressive symptoms and the Premenstrual Symptoms Screening Tool (PSST) to evaluate the presence and severity of PMS. Individuals who meet the criteria for moderate to severe PMS based on the PSST will be considered eligible for further participation. At this stage, informed consent will be obtained. During the second visit, which occurs on the 1st or 2nd day of the subsequent menstrual cycle, the screening process will begin. This is followed by an initial Google Meet session at the same phase of the following cycle to confirm ongoing eligibility and provide further study orientation. The third visit (baseline) will be on 1st to 2nd day of the participant’s menstrual cycle, during which assessments using the Daily Record of Severity of Problems (DRSP), Quality of Life Enjoyment and Satisfaction Questionnaire (Q-LES-Q), and Sheehan Disability Scale (SDS) will be conducted. The intervention begins at the fourth visit (aligned with the 1st to 2nd day of the second menstrual cycle), where participants will be randomly assigned to receive either Cognitive Behavioral Therapy (CBT) combined with *Brahmi* tablets (interventional group) or CBT with placebo tablets (comparator group). CBT sessions will be given on the 5*^th^*, 12*^th^*, 19*^th^* and 26*^th^* day for 2 menstrual cycles with total of eight sessions. A final Google Meet follow-up will be conducted during the 1st to 2nd day of the fifth menstrual cycle to assess outcomes and gather participant feedback.

The schedule of visit chart is mentioned in Table 1. It explains the follow-up visits across four menstrual cycles during the study.

**TABLE 1 T1:** Schedule of visit chart.

Activity/assessment	1^st^ visit (history taking, PSST assessment)	2^nd^ visit (start screening 1^st^ to 2^nd^ day menstrual cycle)	G Meet (1^st^ to 2^nd^ day of next menstrual cycle)	3^rd^ visit Baseline visit (1^st^ to 2^nd^ day of menstrual cycle)	4^th^ visit (1^st^ to 2^nd^ day of 2^nd^ menstrual cycle)	G Meet (1^st^ to 2^nd^ day of 5^th^ menstrual cycle)
Personal history, socio-demographic data, and menstrual history						
Patient health questionnaire-PHQ-9 depression scale assessment						
Pre-Menstrual Syndrome Screening Tool (PSST) assessment						
Informed consent						
(DRSP) scale (given only to the participants diagnosed as moderate to severe PMS by PSST) assessment						
14 Q-LES-Q assessment						
Sheehan Disability Scale (SDS) assessment						
Intervention (CBT with *Brahmi* tablet to Interventional group and CBT with placebo tablet to comparator group. CBT sessions will be given on the 5^th^, 12^th^, 19^th^ and 26^th^ day for 2 menstrual cycles)						
Feedback on the study and intervention						

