### 3.3 Eligibility criteria

Participants must give written, informed consent before participating in any study procedures.

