### 4.6 Data collection methods

#### 4.6.1 Pre-screening (demographic data collection)

Before any assessments, participants will fill out a Google Form to provide demographic information and basic eligibility details. The responses will be transcribed into Microsoft Excel for documentation and initial screening purposes.

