#### 4.6.2 Initial screening

Participants presenting with PMS symptoms will undergo initial screening using the Premenstrual Symptoms Screening Tool (PSST) and PHQ-9 during a single visit at recruitment (baseline, before Cycle 1). The assessment will be done using paper-pencil in English, and the scores will be recorded in Microsoft Excel.

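### Section 3.3 requires written consent before any study procedure, but section 4.2.1 takes it only after the history, PHQ-9 and PSST are done and PSST eligibility is decided

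*Protocol article*

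**What the plan says.** The governing rule is in section 3.3: "Participants must give written, informed consent before participating in any study procedures".

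Section 4.2.1 describes the first visit in four steps:

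1. "During the first visit, personal history, socio-demographic information, and detailed menstrual history will be recorded".
2. "Participants will also complete the Patient Health Questionnaire-9 (PHQ-9) to assess depressive symptoms"; the same sentence adds the PSST.
3. "Individuals who meet the criteria for moderate to severe PMS based on the PSST will be considered eligible for further participation".
4. "At this stage, informed consent will be obtained".

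Section 4.6.2 describes the same assessments from the data-collection side: "Participants presenting with PMS symptoms will undergo initial screening using the Premenstrual Symptoms Screening Tool (PSST) and PHQ-9 during a single visit at recruitment". It adds that they are done on paper and that the scores go into Excel.

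An online form comes before all of this. Section 4.6.1 says: "Before any assessments, participants will fill out a Google Form to provide demographic information and basic eligibility details". It continues: "The responses will be transcribed into Microsoft Excel for documentation and initial screening purposes".

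**The concern.** The rule in 3.3 has no exception for screening, and the sequence in 4.2.1 ties consent to a positive PSST result. If the questionnaires are study procedures, a site cannot follow both sections.

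What is at stake is participant protection and not inference. The PHQ-9 is used to exclude moderate to severe depression (section 3.3.1), so a sensitive mental-health score is obtained and recorded before the woman has agreed to take part in anything. A woman who does not reach the PSST threshold leaves a record behind and, under 4.2.1, is not asked for consent at all.

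**Working it through.** No arithmetic applies. The question is the order of events and whether the early steps count as study procedures, so the sections are set side by side.

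**Order of events, reconstructed from the text**

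1. Online form with demographic and eligibility items (4.2.3, 4.6.1).
2. First visit: personal, socio-demographic and menstrual history (4.2.1).
3. First visit: PHQ-9 and PSST (4.2.1, 4.6.2).
4. First visit: eligibility decision on the PSST (4.2.1).
5. First visit: informed consent (4.2.1).
6. From the second visit: DRSP diaries over two cycles, then baseline, randomisation and treatment (4.2.1, 4.6.3).

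Section 3.3 puts consent ahead of every study procedure. Section 4.2.1 puts it fifth. The rows of Table 1 run in the same order as 4.2.1, with consent below the PHQ-9 and PSST. The cell marks are not legible in the text available, and row order alone does not fix the order within a visit, so this is weak support only.

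**Are the PHQ-9 and PSST study procedures?** On the protocol's own terms, yes:

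- Section 3.3.1 makes a PHQ-9 score below 10 and a PSST diagnosis of moderate to severe PMS inclusion criteria.
- Section 4.6.2 calls them screening and has the scores recorded.
- Table 2, the schedule of assessments and data collection, gives them their own row.

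**Does another section put consent first?** No:

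- Section 4.6.5 and Table 2 have the consent documents handed over before enrolment, with a timeline entry ahead of the first cycle. The PSST and PHQ-9 carry the same timeline entry, so it does not place consent before them. Handing over a form is also not the same as obtaining consent.
- Section 8.2 describes the consent discussion but gives no timing relative to screening.
- Section 4.2.3 reports ethics approval of the awareness activities and recruitment channels. It mentions no consent waiver and no separate screening consent for either questionnaire.

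**Who is affected?** Every woman assessed at visit 1 gives history, PHQ-9 and PSST data before consent. Women who pass the PSST consent later at that visit. Women who fail it reach no consent step. Section 4.2.1 does not say what happens to a woman who passes the PSST but scores 10 or more on the PHQ-9.

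**The case against.** The best defence is that the first visit is ordinary clinic intake. Section 4.2.1 has screening start at the second visit, after consent, and the Table 1 column header agrees. Sections 4.2.3 and 4.3 describe an outpatient consultation before a woman is considered for enrolment. On that reading trial procedures begin only after consent, and the fault is loose use of the word screening.

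This shows that the terminology is inconsistent, but it does not remove the conflict. Section 4.6.2 and Table 2 label the PSST and PHQ-9 as initial screening, their results decide eligibility, and the scores are kept as trial data.

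Other parts of the defence do stand, and they limit what can be claimed. A reader might infer the following, none of which the document supports:

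- **That every screen failure goes without consent.** Women who fail at the two-cycle DRSP confirmation have already consented under 4.2.1.
- **That the number of women affected can be worked out from the PMS prevalence range in section 1.1 (14.3% to 74.4%).** That range is reported prevalence of PMS in India, not the PSST pass rate for moderate to severe PMS. The women at visit 1 are also pre-selected for symptoms by the online form.
- **That the online form breaches 3.3 in the same way.** It sits under recruitment, and whether it is a study procedure is arguable. Its wording is not shown and it may already carry a consent statement. Section 4.6.1 says only that responses go into Excel, not that they enter the trial's analysis dataset.
- **That the screening denominator would be lost.** No rule discards screen-failure data, no feasibility outcome is listed in section 2.1 or section 4, and reporting how many were screened needs counts, not individual health records.

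**Conclusion.** The conflict between 3.3 and 4.2.1 is real, and the text is wrong as written. Following 4.2.1 breaches the protocol's own consent rule for all women assessed at visit 1, that is, for all PHQ-9 and PSST records. How many women that is cannot be derived from the document.

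The conclusion rests on treating the PHQ-9 and PSST as study procedures, which 3.3.1, 4.6.2 and Table 2 support. It does not depend on the status of the online form or on the missing marks in Table 1.

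The point concerns ethics and conduct. Eligible women consent before diaries, baseline, randomisation and treatment, so no effect estimate, error rate or sample-size figure changes. It should still be corrected, because it bears on participant protection and is cheap to put right.

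**What to change.** In section 4.2.1, move written consent to the start of the first visit, before the history, PHQ-9 and PSST. If full trial consent is thought premature at that point, use a short written screening consent there and take trial consent after the PSST. Check Table 1 and align it if its marks or order differ.

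As a secondary step, confirm that the online form opens with a brief consent statement covering the collection and storage of the answers, and add one if it does not.

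The cost is a reordered visit, possibly one added line on a form, and a few more consent discussions with women who then screen out. No outcome, visit date, sample size or analysis changes.

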### 3.4 Interventions

The study intervention will span two menstrual cycles. Participants in the intervention group will receive one-to-one online Cognitive Behavioral Therapy (CBT) sessions, combined with a 500 mg *Brahmi* (Bacopa monnieri) tablet administered once daily after (31, 32) meals with lukewarm water. (33, 34) The control group will receive identical CBT sessions alongside a 500 mg placebo tablet containing inert excipients (dicalcium phosphate, talc, and starch), also taken once daily after food with lukewarm water. Oral medications will be withheld during the menstrual bleeding period for both groups.

The *Brahmi* and placebo tablets were procured from a GMP-certified manufacturer and underwent quality control and analysis to ensure safety, potency, and consistency. Both *Brahmi* and placebo tablets are film-coated to provide uniform appearance, stability, and ease of administration, with the placebo identical in color, shape, and packaging to maintain the double-blind design of the exploratory study.

Cognitive Behavioral Therapy (CBT) sessions will be conducted by two certified CBT therapists, both of whom hold a Master’s degree in Counseling Psychology and formal certification in CBT from accredited institutions. Each therapist has over 2 years of clinical experience in delivering CBT for stress- and mood-related disorders in outpatient settings.

Sessions will be delivered individually (one-on-one) to allow personalized assessment and guidance, ensuring that the intervention is tailored to each participant’s needs. In the event that one therapist is unavailable, the other will continue the intervention without disruption to maintain consistency.

A total of eight sessions will be delivered over two menstrual cycles, on the 5th, 12th, 19th, and 26th days of each cycle, with each session lasting approximately 45 min to 1 h. The CBT protocol is adapted from a previously published study on PMS and includes:

Protocol for Cognitive Behavioral Therapy sessions adapted from a standardized published study on CBT for PMS (7):

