### 4.7 Exploratory statistical analysis

Exploratory statistical analysis will primarily explore the potential impact of Cognitive Behavioral Therapy (CBT) combined with either *Brahmi* (Bacopa monnieri) tablets or placebo in participants with moderate to severe Premenstrual Syndrome (PMS). Outcome measures include the Daily Record of Severity of Problems (DRSP), Quality of Life Enjoyment and Satisfaction Questionnaire (Q-LES-Q), and Sheehan Disability Scale (SDS), assessed at three time points: baseline (third visit), during treatment (fourth visit), and post-treatment (fifth cycle follow-up). Analyses will be descriptive, focusing on effect size estimates and 95% confidence intervals to provide insights into the direction and magnitude of observed effects. P values will be presented descriptively without inferential claims, in line with the exploratory nature of the study. Where appropriate, repeated measures approaches such as ANOVA or mixed-effects models may be applied to summarize changes over time and between groups, with emphasis placed on effect size interpretation to generate preliminary signals for future confirmatory research.

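### The participant timeline starts treatment at the fourth visit, which the analysis section treats as mid-treatment and which does not fit treatment in Cycles 3 and 4

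*Protocol article*

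**What the plan says.** All references are to the protocol article.

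- **Section 4.2.1 (Participant timeline):** "The intervention begins at the fourth visit (aligned with the 1st to 2nd day of the second menstrual cycle"). Participants are randomised at this visit. The third visit is the baseline assessment, on day 1 or 2 of a cycle that is not numbered. The section then says: "A final Google Meet follow-up will be conducted during the 1st to 2nd day of the fifth menstrual cycle".
- **Table 1:** the text introducing it says "It explains the follow-up visits across four menstrual cycles during the study", and its column heading for the fourth visit reads "4^th^ visit (1^st^ to 2^nd^ day of 2^nd^ menstrual cycle").
- **Sections 4.6.3 and 4.6.4, and Table 2:** daily DRSP screening takes up Cycles 1 and 2; Cycles 3 and 4 are the interventional phase. Table 2 has SDS and Q-LES-Q-SF completed on day 1 or 2 of Cycles 3 and 4, each recalling the previous cycle.
- **Section 4.7 (Exploratory statistical analysis):** DRSP, Q-LES-Q and SDS are "assessed at three time points: baseline (third visit), during treatment (fourth visit), and post-treatment (fifth cycle follow-up").
- **Section 3.4 (Interventions):** "A total of eight sessions will be delivered over two menstrual cycles, on the 5th, 12th, 19th, and 26th days of each cycle". Tablets are not taken during menstrual bleeding in either arm.
- **Section 4.1 (primary outcomes):** "Daily Record of Severity of Problems (DRSP) across two intervention cycles", and Q-LES-Q "Short Form (Q-LES-Q SF 12) from baseline to post-intervention".

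**The concern.** Section 4.2.1 is an operative instruction: it tells site staff at which visit to randomise and start treatment. It names the fourth visit. The analysis section treats that same visit as already on treatment, and the data-collection sections have treatment starting in Cycle 3, straight after two screening cycles.

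If staff follow section 4.2.1, the fourth-visit data are collected before treatment has had any chance to act. The between-arm effect size and 95% confidence interval reported for that time point would contain no treatment effect, and any three-point repeated-measures summary would hold two pre-treatment points. Effect sizes and intervals are the stated output of this exploratory trial, so a mislabelled time point matters even without inferential claims. If the fourth visit also falls in Cycle 4, as the visit order suggests, the Cycle 5 assessment would come halfway through CBT.

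**Working it through.** The check is a calendar count. It needs no assumed effect size, standard deviation or correlation.

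**Inputs**
- CBT on days 5, 12, 19 and 26 of two treated cycles: 4 × 2 = 8 sessions (section 3.4).
- Third and fourth visits and the final contact on day 1 or 2 of a cycle (section 4.2.1).
- Two DRSP screening cycles before eligibility is confirmed (sections 3.3.1 and 4.6.3).
- Final contact in Cycle 5 (section 4.2.1).
- Visit order in section 4.2.1: second visit opens Cycle 1; first online contact opens Cycle 2; third visit is then Cycle 3 and fourth visit Cycle 4. The last two cycle numbers are inferred from the order, not stated.

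**Step 1. Section 4.2.1 as written, whichever cycle the fourth visit is in.** The gap from the fourth visit to the first CBT session is 5 − 2 = 3 to 5 − 1 = 4 days. Sessions before the fourth-visit score: 0 of 8. Tablets are withheld during bleeding, so essentially none have been taken by day 1 or 2. SDS and Q-LES-Q recall the previous cycle, which would be untreated.

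**Step 2. Try each possible start cycle.**

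| Treatment starts | Treated cycles | Screening cycles complete at start | CBT sessions before the Cycle 5 contact | Treated cycles covered by Cycle 3–4 diaries |
|---|---|---|---|---|
| Cycle 2 (ordinal counted from screening) | 2 and 3 | 1 of 2 | 8 of 8 | 1 of 2 |
| Cycle 3 | 3 and 4 | 2 of 2 | 8 of 8 | 2 of 2 |
| Cycle 4 (fourth visit by visit order) | 4 and 5 | 2 of 2 | 4 of 8 | 1 of 2 |

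A Cycle 2 start breaks the two-cycle screening requirement and precedes the baseline visit. A Cycle 4 start leaves half the sessions undelivered at the post-treatment assessment and contradicts section 4.6.4. Only a Cycle 3 start fits sections 3.3.1, 4.6.3, 4.6.4, Table 2 and the Cycle 5 contact together.

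**Step 3. Compare with the section 4.7 labels.**

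| Time point in section 4.7 | Sessions delivered, Cycle 3 start | Sessions delivered, Cycle 4 start (inferred) |
|---|---|---|
| Third visit, baseline | 0 of 8 | 0 of 8 |
| Fourth visit, on treatment | 4 of 8 | 0 of 8 |
| Cycle 5, post-treatment | 8 of 8 | 4 of 8 |

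The Cycle 3 column matches all three labels. It also fits the previous-cycle recall in Table 2: the Cycle 3 assessment recalls an untreated cycle and the Cycle 4 assessment recalls the first treated cycle. But treatment then starts at the third visit, not the fourth, so the sentence in section 4.2.1 is the one that does not fit.

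**The case against.** The strongest counter-argument is that this is one misplaced clause in otherwise consistent text. The second menstrual cycle in section 4.2.1 and Table 1 can be read as the second treated cycle, which is Cycle 4; on that reading the Table 1 heading and the section 4.7 label are both right. That is fair as far as the ordinal goes. It does not rescue the sentence, because the intervention cannot begin, and participants cannot be randomised, in the second treated cycle.

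Other points on that side, and what stands of them:

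- **Small consequence.** This largely stands. Neither primary outcome as defined in section 4.1 uses the fourth visit, the analysis is descriptive, repeated-measures methods are optional, and both arms share one calendar, so no between-arm bias arises. The primary outcomes are exposed only if the start falls in Cycle 4, which is inferred.
- **Table 1 might settle it.** The cell marks are not legible in the text available, so only the column headings are used here. No set of marks could make the prose of section 4.2.1 agree with sections 4.6.4 and 4.7.
- **Two sections are being combined.** True: section 4.2.1 itself lists no outcome assessment at the fourth visit; section 4.7 does. The conflict lies precisely between the two.
- **The gap between baseline and randomisation may be intended.** The document does not exclude this. If so, the error lies elsewhere, and sections 4.6.4, 4.7, Table 2 and the Cycle 5 contact would all need changing.
- **Section 4.4 also times allocation,** with packages handed out at enrolment. This is correct, and it should be aligned in the same edit.

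**Conclusion.** The concern holds. Section 4.2.1 cannot be reconciled with section 4.7 and with the treatment cycles in section 4.6.4 and Table 2. Followed literally, it makes the fourth-visit assessment a pre-treatment measurement, with 0 of 8 CBT sessions delivered and the first still 3 to 4 days away, while section 4.7 reports it as on-treatment. The weight of the text favours a Cycle 3 start, with 0, 4 and 8 sessions before the three time points; in that case the section 4.7 labels are right and the section 4.2.1 sentence is wrong.

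The counts rest only on the stated session days and contact days. The worse scenario, in which the Cycle 5 assessment comes after 4 of 8 sessions and the diaries cover 1 of 2 treated cycles, depends on placing the fourth visit in Cycle 4 by visit order. Because the section 4.1 primary outcomes do not use the fourth visit and the analysis is descriptive, this is something to correct, not a threat to the trial as a whole.

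**What to change.** Rewrite the timeline as one calendar with numbered cycles:

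- **Third visit, day 1 or 2 of Cycle 3:** baseline assessment first, then randomisation and start of treatment.
- **Fourth visit, day 1 or 2 of Cycle 4** (the second treated cycle): mid-treatment assessment.
- **Final contact, day 1 or 2 of Cycle 5:** post-treatment assessment.

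Use the same cycle numbers in the Table 1 column headings, and name the section 4.7 time points by cycle and day. Add the Cycle 5 Q-LES-Q and SDS assessment to Table 2, so that it agrees with sections 4.2.1 and 4.7. Check that the package hand-out in section 4.4 refers to the same visit.

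The cost is protocol wording: one sentence in section 4.2.1, the Table 1 headings, the time-point names in section 4.7, one line in Table 2 and, if needed, a phrase in section 4.4. No new contact is required, since the Cycle 5 follow-up is already planned, and the sample size of 46 is unaffected. If sites are already randomising at the fourth visit, the change is procedural as well, and staff must be told of it.
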